## INTRODUCTION

Postoperative patient management after liver transplantation is complex and
challenging, as there is an increased risk to the viability of the graft and to the
survival of the patient.^(1)^ In this
scenario, hemodynamic optimization may be a determining factor in the evolution of
the clinical condition.

Renal dysfunction is one of the most frequent postoperative complications after liver
transplantation and is considered the most important predictor of poor long-term
outcome,^(2)^ as it is
associated with higher mortality^(3)^
and impacts the quality of life, as 18.1% of these patients will have a renal
clearance < 30mL/minute/1.73m^2^ within 5 years.^(4)^ This dysfunction is related to a
combination of preoperative (previous renal function, hepatorenal syndrome and
diuretics), intraoperative (ischemia‒reperfusion injury, shock and bleeding) and
postoperative events (nephrotoxic drugs, water balance and hemodynamic
optimization).^(4)^

One of the classical drivers of renal dysfunction is hypoperfusion, which is closely
linked to mean arterial pressure (MAP).^(5)^ The classic target of MAP > 65mmHg is described as the
safety threshold,^(6,7)^ although a trial employing higher MAP levels showed
lower renal dysfunction in certain subgroups of patients with sepsis.^(8)^ In surgical patients, hypotension
is associated with a higher incidence of acute renal dysfunction, and this risk
increases with the length of the insult.^(9,10)^ A reduction in
other postoperative complications has been observed following hemodynamic
optimization for achieving a MAP closer to the patient’s baseline.^(11)^

In the specific scenario of liver transplantation, retrospective data adjusted for
the propensity score inferred the best renal outcome with a MAP >
90mmHg,^(12)^ while a
physiological evaluation indicated that a reduction in renal blood flow occurs below
a MAP threshold of 75mmHg.^(13)^

Preventing renal dysfunction in the postoperative period may represent an important
way to improve short- and long-term patient outcomes, with blood pressure being a
possible therapeutic target. However, there is no definition of the best blood
pressure target and the exact relationship between different blood pressure levels
and renal outcome. In addition, there are currently few randomized clinical trials
in liver transplant intensive care, during which renal dysfunction is more
frequent.^(12)^ Considering

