### Randomization and blinding

Patients will be randomized within 2 hours of ICU admission after liver
transplantation using a simple 1:1 allocation sequence without group
stratification. The randomization will be performed electronically by the
randomization tool of the Redcap® system. The randomization sequence will
be generated *online* and entered into the system by a staff
member who will not participate in the participant tracking process, in
obtaining informed consent from the patient or in the clinical management of the
cases. The researcher will also not participate in the evaluation of the study
outcome data in order to ensure compliance with the allocation concealment
process.

As the interventions in both groups are based on target MAP levels to be followed
by the professionals involved in the care, the authors chose not to blind the
interventions, which, although possible, would be complex to perform in the
center in question. However, the professional responsible for collecting the
outcome data will be an external research nurse, with no affiliation with the
institution where the study is conducted and who is not involved with the care
offered to each patient. The same care will be taken to hire the statistician
who will analyze the results, ensuring that he or she will not be aware of the
allocated groups. To minimize the risk of bias, an objective primary outcome was
chosen based on test results measured by a certified laboratory.

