### Data collection

The following data will be collected from all patients: name, sex, age, race,
height, weight, hospital identification number, date of birth, etiological
diagnostic indicator of transplantation, pretransplantation Model for End-stage
Liver Disease (MELD) score, origin before transplantation (ICU, ward or home),
comorbidities (diabetes mellitus, heart failure, arterial hypertension,
nondialytic chronic renal failure, active cancer, previous stroke or transient
ischemic attack or immunosuppressive therapy in the last 30 days before
surgery), preoperative creatinine, donor risk index (DRI) and use of nephrotoxic
drugs in the week before transplantation.

The following intraoperative data will also be collected: anesthesia time, total
and cold ischemia time of the liver graft, presence of ischemia‒reperfusion
syndrome, time of admission to the ICU, use of blood products, antibiotic
prophylaxis, initial value of arterial lactate, peak arterial lactate, final
value of arterial lactate, use of basiliximab, use of fluids, type of fluids,
episodes of intraoperative hypotension and loss of fluids.

The following postoperative data will also be collected: length of hospital stay
after transplantation; length of stay in the ICU; time of mechanical
ventilation; duration of vasopressor use and maximum vasopressor dose; need for
renal replacement therapy; need for postoperative transfusion; primary graft
dysfunction; secondary graft dysfunction; need for retransplantation; surgical
site infection; Sequential Organ Failure Assessment (SOFA) score on admission to
the ICU; D1, D3 and D7; daily creatinine, to evaluate the presence of acute
kidney failure (AKI) in the first 28 days after transplantation or until
hospital outcome if this occurs before the described period; admission and
48-hour urinary NGAL; presence of surgical site infection in the first 7 days
after transplantation; arrhythmias requiring chemical or electrical treatment in
the first 7 days after transplantation; diagnosis of acute coronary syndrome in
the first 7 days after transplantation; volume of crystalloids infused in the
first 24 hours after surgery; volume of colloids infused in the first 24 hours
after surgery; diuresis in the first 24 hours after surgery; drainage output in
the first 24 hours after surgery; presence of major bleeding in the first 24
hours after surgery; need for transfusion in the first 24 hours after surgery;

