### Sample size calculation

Based on the primary outcome incidence of 73.7% (acute renal dysfunction within 7
days) obtained from a database of the same population and location, 174 patients
will be required to demonstrate an absolute reduction of 20% in the primary
outcome, with a power statistic of 80% and alpha of 5%. The data used for this
calculation were obtained by calculating the incidence of AKI based on an
increase in serum creatinine by 1.5 times the baseline value. The criterion used
to choose the effect (20% absolute reduction in the AKI outcome) was chosen
based on the principle of clinical relevance. All patients selected for
transplantation will be evaluated regarding the inclusion and exclusion criteria
and will be informed of the study in a standardized way if able to
participate.

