### Statistical analysis

The analyses will be performed according to the “intention-to-treat” principle;
all randomized patients will be included in the analysis according to the
treatment group to which they were randomly assigned. Summary statistics per
group, with treatment effects, 95% confidence intervals and p values, will be
presented for the primary and secondary outcomes. Continuous variables will be
tested for normality using the Shapiro‒Wilk test after graphic analysis by
histogram. Parametric continuous variables between two groups will be compared
with the unpaired *t* test and within the same group with the
paired *t* test. If analysis among more than two groups is
required, analysis of variance (ANOVA) will be used. Nonparametric continuous
variables will be evaluated using the Wilcoxon test or the Mann‒Whitney U test
between two groups and the Kruskal‒Wallis test between three or more groups.
Categorical variables will be evaluated using the chi-square test or Fisher’s
exact test, as appropriate. P values < 0.05 will be considered statistically
significant. The outcomes of hospitalization-free days or renal dysfunction over
time will be calculated based on the 7- and 28-day follow-up, respectively,
using Cox regression models. The calculations of survival curves will be
performed with the Kaplan‒Meier method. For the statistical analysis of
outcomes, the results will be adjusted for previous renal function, and logistic
regression will be used to adjust for other confounding factors that generate
inconsistency in the baseline that were not corrected by the randomization of
the study (use of nephrotoxic drugs, maximum tacrolimus level in the first week,
intraoperative fluid balance and intraoperative major bleeding). No statistical
adjustments will be provided for multiple comparisons in the case of secondary
outcomes, and therefore, we suggest that these be interpreted as exploratory
analyses.

The existence of missing data will be described in the publication and managed
with simple exclusion from the analysis. For this study, no interim analyses are
foreseen.

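### Adjustment for the primary outcome omits MELD, reperfusion syndrome and intraoperative hypotension, which are collected and fixed before randomisation; prespecifying such covariates could add about 0 to 8 points of power

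*Protocol article*

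**What the plan says.** All places are in the protocol article.

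- **Statistical analysis.** Without condition, "the results will be adjusted for previous renal function". Logistic regression then adjusts for other factors where randomisation has left them unbalanced. Four are named: nephrotoxic drugs, maximum tacrolimus level in the first week, intraoperative fluid balance and intraoperative major bleeding. Missing data are handled by leaving the patient out.
- **Randomization and blinding.** Allocation is a "simple 1:1 allocation sequence without group" stratification, made up to 2 hours after ICU admission.
- **Introduction.** The causes listed for renal dysfunction include previous renal function and then "diuretics), intraoperative (ischemia‒reperfusion injury, shock and bleeding) and" postoperative events.
- **Data collection.** The variables recorded include the pretransplant MELD score, total "and cold ischemia time of the liver graft, presence of ischemia‒reperfusion" syndrome, episodes of intraoperative hypotension, and urinary NGAL at admission and 48 hours.
- **Sample size calculation.** 174 patients, for a 20-point absolute reduction from 73.7%.

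**The concern.** The plan names its covariates, so the choice can be judged as written. Of the three intraoperative causes in the Introduction, bleeding reaches the conditional list, while ischaemia-reperfusion injury and shock reach neither list. The variables that would represent them are on the case report form and are settled when surgery ends, before randomisation. MELD is also recorded before transplantation and not used.

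An imbalance trigger responds to chance differences between arms. It does not secure a planned gain in precision, because a prognostic covariate narrows the comparison whether or not it happens to be unbalanced. With unstratified allocation the design contributes no prognostic balance of its own, so precision has to come from the analysis. At stake is some power in a trial sized at about 80% with no stated allowance for loss.

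**Working it through.** **1. The plan's own figure.** Inputs from Sample size calculation: the control rate ("Based on the primary outcome incidence of 73.7" per cent), the target difference of 20 points, the total of 174, and the error rates ("outcome, with a power statistic of 80% and alpha of 5" per cent). The intervention rate is therefore 0.737 − 0.20 = 0.537. Sidedness is not stated; two-sided is assumed because it reproduces the total.

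Unpooled formula: n per arm = (1.960 + 0.842)² × [0.737 × 0.263 + 0.537 × 0.463] / 0.20² = 7.85 × 0.4425 / 0.04 ≈ 86.8, so 87 per arm and 174 in total. The figure reproduces. An unadjusted test at 87 per arm has power 78.8% (pooled normal formula) or 79.1% (exact calculation for the chi-square test). The shortfall from 80% reflects the choice of formula.

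**2. The right comparator.** The plan already adjusts for previous renal function, so gains are counted from that model. If that covariate explains R² = 0.05 of the outcome (assumed), the effective size is 87 / (1 − 0.05) = 91.6 per arm and power is 80.9%.

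**3. Analytic gain.** With added R² from further covariates, effective n per arm = 87 / (1 − 0.05 − added R²):

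| Added R² (assumed) | Power |
|---|---|
| 0 | 80.9% |
| 0.05 | 83.0% |
| 0.10 | 85.0% |
| 0.15 | 87.1% |
| 0.20 | about 89% |

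**4. Simulation.** 174 patients, 4,000 trials per scenario, marginal rates 0.737 and 0.537. Previous renal function has log-odds 0.5 per SD. Four extra independent covariates have the strength shown. The test is the logistic treatment coefficient at 5% two-sided.

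| Strength of each extra covariate (log-odds per SD) | AUC of all covariates | Previous renal function only | With four extra |
|---|---|---|---|
| None (0) | 0.64 | 80.2% | 80.3% |
| Weak (0.2) | 0.67 | 80.3% | 81.1% |
| Moderate (0.4) | 0.73 | 80.6% | 83.9% |
| Strong (0.6) | 0.79 | 80.0% | 87.8% |

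Type I error of the adjusted models was 4.4% to 5.4%. The Monte Carlo standard error of each power figure is √(0.8 × 0.2 / 4,000) ≈ 0.6 points. Three extra covariates (without NGAL), or covariates that overlap with one another, would give less at the same individual strength.

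**5. Cost of missing covariates.** Under simple exclusion with a share m missing, the gain vanishes when 87(1 − m) / (1 − 0.05 − 0.10) = 87 / (1 − 0.05), that is m = 1 − 0.85/0.95 ≈ 10.5% for an added R² of 0.10. Against no adjustment at all, 10% missing cancels a total R² of 0.10: 87 × 0.9 / 0.9 = 87, power 78.8%.

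**6. Model size.** The mean event rate is (0.737 + 0.537)/2 = 0.637, so expected non-events are 174 × 0.363 ≈ 63. Treatment plus four covariates gives 63/5 = 12.6 per parameter; with NGAL, 63/6 = 10.5. Adding the four conditional factors on top would give 63/10 = 6.3, which is why the fixed set should replace that list.

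**The case against.** The strongest reply is that nothing here is wrong. The plan prespecifies adjustment for a sensible covariate, and asking for more is a preference about efficiency. A condensed article may also leave the full model to a document not shown. The first part stands as to severity: this is lost efficiency. The second stands only in part, because the article lists its covariates rather than staying silent. If a full protocol or analysis plan fixes a different set, the point lapses.

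Several stronger readings are tempting and are not supported:

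- **That previous renal function is the only covariate.** It is the only unconditional one. Four others can enter, including intraoperative bleeding and fluid balance.
- **That strong predictors are being ignored.** No section gives a prognostic figure for any of them. The Introduction supports ischaemia-reperfusion injury and shock qualitatively and mentions neither MELD nor NGAL. The exclusion of persistent refractory shock also removes some of the variation.
- **That power would rise from 79%.** That starting point ignores the adjustment already planned.
- **That admission NGAL is a pre-randomisation variable.** Randomisation may follow admission by up to 2 hours, the intervention is said to begin on admission, and no section places the sample before allocation. Admission NGAL also belongs to a secondary outcome.
- **That the change is free.** Under simple exclusion, missing covariates can cancel the gain (step 5).

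**Conclusion.** The point holds as a recommendation on efficiency. Plausible prognostic variables that are collected and fixed before randomisation are outside both adjustment lists, against the article's own account of what causes the outcome. Prespecifying such covariates would change power by about 0 to 8 points: from about 80% to about 81–88% under weak to strong prognosis, and not at all if they carry no information. These figures assume the design event rates, complete covariates, four independent added covariates and prognostic strengths that the documents do not supply. The planned primary analysis remains valid without the change.

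**What to change.** For the primary outcome, replace the imbalance-triggered list with one short set, named in advance and used regardless of observed balance: previous renal function, MELD, ischaemia-reperfusion syndrome and intraoperative hypotension. Add admission urinary NGAL only if the sample is confirmed to precede allocation. This also removes the first-week tacrolimus level, which is measured after randomisation, from the primary model.

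Report a standardised (marginal) risk difference with its 95% confidence interval. A logistic coefficient alone is a conditional odds ratio, whereas the trial is sized on an absolute difference. For missing baseline covariates, use simple imputation or a missing-indicator so that no randomised patient is dropped.

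Fix this before outcomes are examined by arm. It needs new wording and no new data. The cost is a slightly larger model and one added rule for missing covariates.

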**Conclusion:**

If a 20% reduction in the absolute incidence of renal dysfunction in the
postoperative period of liver transplantation is achieved with higher target
mean arterial pressure in the first 24 hours, this would represent an
inexpensive and simple therapy for improving current outcomes in the
management of liver transplant patients.

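### The adjusted analysis of the primary outcome names logistic regression but no effect scale, although the trial is sized and framed on an absolute risk reduction

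*Protocol article*

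**What the plan says.** Three places in the protocol article bear on the scale of the effect.

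- **Sample size calculation.** The control incidence comes from local data: "Based on the primary outcome incidence of 73.7% (acute renal dysfunction within 7" days. The stated number of patients "will be required to demonstrate an absolute reduction of 20% in the primary" outcome. The section adds that this absolute effect was chosen for its clinical relevance.
- **Abstract, Conclusion.** The practical message is conditional on the same quantity: "If a 20% reduction in the absolute incidence of renal dysfunction in the" postoperative period.
- **Statistical analysis.** Per-group summaries are promised, with treatment effects, confidence intervals and p values, but no effect measure is named. Categorical variables are compared by chi-square or Fisher's exact test. Results are then to be adjusted for previous renal function, and logistic "regression will be used to adjust for other confounding factors that generate" inconsistency at baseline. Four such factors are listed, one of which is the highest tacrolimus level in the first week. Cox models are named only for two outcomes followed over time, so logistic regression is the only adjusted model named for a binary outcome. No step turns its result into an absolute difference.

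**The concern.** The trial asks by how many percentage points the higher pressure target lowers the incidence of renal dysfunction. A logistic model answers, by default, with a conditional odds ratio. For a rare outcome the odds ratio would at least approximate the risk ratio. With nearly three quarters of control patients expected to have the event, it does not.

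The adjusted estimate is part of the planned report. If it appears only as an odds ratio, a reader cannot set it beside the 20-point effect used for sizing without a further calculation. The odds ratio also has a property that the risk difference lacks: adding a prognostic covariate moves it away from 1 even when the arms are perfectly balanced (non-collapsibility). Because the scale is left open, the choice among three very different-looking numbers could also be made after the data are seen.

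**Working it through.** **Inputs**

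- Control risk p1 = 0.737, absolute reduction 0.20, hence p2 = 0.537 (Sample size calculation).
- Power 80%, alpha 5%, total 174 (same section). Sidedness is not stated; two-sided is assumed here.
- Allocation 1:1 (Randomization and blinding), so 87 per arm.

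**1. Reproducing the plan's own figure.** Normal approximation with unpooled variance:

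n per arm = [p1(1−p1) + p2(1−p2)] × (1.960 + 0.842)² / 0.20²
= (0.1938 + 0.2486) × 7.849 / 0.04 = 86.8, rounded up to 87, total **174**.

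The figure reproduces exactly, which confirms that the design quantity is a difference between two proportions. (The pooled-variance formula gives 180.)

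**2. The same design effect on three scales**

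| Measure | Calculation | Value |
|---|---|---|
| Risk difference | 0.737 − 0.537 | 20 points |
| Risk ratio | 0.537 / 0.737 | 0.73 |
| Odds ratio | (0.537/0.463) / (0.737/0.263) = 1.160 / 2.802 | 0.41 |

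The relative reduction is 27% in risk and 59% in odds.

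**3. An odds ratio alone does not fix the absolute effect.** With control odds o = p/(1−p), the treated risk is 0.414·o / (1 + 0.414·o). The control risks below, apart from 73.7%, are assumed for illustration.

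| Control risk | Absolute reduction at odds ratio 0.414 |
|---|---|
| 50% | 20.7 points |
| 60% | 21.7 points |
| 73.7% | 20.0 points |
| 80% | 17.7 points |
| 90% | 11.2 points |

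**4. Non-collapsibility (covariate strength is assumed; the article gives none).** Let X be a standard normal covariate, balanced between arms, with log-odds s per SD. For each arm, solve for the intercept a_j so that the average of expit(a_j + sX) equals p_j. The conditional odds ratio is exp(a_2 − a_1).

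| s per SD | Conditional odds ratio | Marginal risk difference |
|---|---|---|
| 0.5 | 0.39 | 20 points |
| 1.0 | 0.35 | 20 points |
| 1.5 | 0.29 | 20 points |

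The last column is constant by construction: the marginal risks are held at 73.7% and 53.7%.

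**5. Is power affected?** At 87 per arm, power is 78.8% for the pooled two-proportion test and 77.5% for an unadjusted Wald test on the log odds ratio. The two are close, so the issue is the reporting scale and not power.

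**The case against.** The strongest reply is that nothing in the article is wrong. It never mentions an odds ratio. It names a model and promises treatment effects, and a logistic model can yield a risk difference. The effect measure of an adjusted analysis is also the kind of detail that a journal article often leaves to the full protocol or analysis plan. This largely stands, and it is why the point is a suggested improvement and not an error. What remains is that the article itself fixes both the absolute design scale and the adjusted model, and leaves the link between them unstated.

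Four stronger readings are tempting, and the document does not support them.

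- **The trial will be decided on a 20-point threshold that the adjusted result cannot meet.** There is no such rule. The 20 points size the trial and frame a conditional sentence in the abstract; the significance criterion is P < 0.05.
- **The benefit will look more than twice as large as it is.** Reading 0.414 as a risk ratio gives 0.737 × 0.414 = 0.305, an apparent fall of 43 points. That needs a reader to mistake an odds ratio for a risk ratio, which the plan does not propose and the promised per-group summaries would expose.
- **A shift from unadjusted to adjusted odds ratio will be taken as corrected imbalance.** No such comparison is planned. The shifts in step 4 rest on assumed covariate strengths, and most are modest beside sampling error: at the design rates with 87 per arm, the standard error of the log odds ratio is √(1/64.1 + 1/22.9 + 1/46.7 + 1/40.3) = 0.325, giving a 95% interval of about 0.22 to 0.78 around 0.41.
- **The sample size or the test is invalid.** Steps 1 and 5 show otherwise.

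The per-group incidences also give the unadjusted risk difference directly, so only the adjusted result is concerned.

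**Conclusion.** The point holds in a limited form. The design and the framing are on the absolute scale; the one adjusted model named for binary outcomes reports by default on the odds scale; and no effect measure is stated. At the design rates the three measures are 20 points, 0.73 and 0.41, figures that rest only on the article's 73.7% and 20-point reduction. Any further movement of the odds ratio through adjustment, to about 0.39 to 0.29, depends on an assumed covariate strength of 0.5 to 1.5 log-odds per SD.

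Severity is low. The unadjusted comparison, the 174 patients and the test of no effect stand. If the full protocol or an analysis plan already names the risk difference for the adjusted analysis, the point is met.

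**What to change.** Add to the Statistical analysis section that the adjusted effect on the primary outcome, and on other binary outcomes analysed by logistic regression, will be reported as a standardised (marginal) risk difference. To obtain it, fit the logistic model, predict each patient's risk under both allocations, average the predictions within each allocation and take the difference. Give a 95% confidence interval by the delta method or bootstrap, with the risk ratio beside it. The odds ratio may be kept as a supplementary figure.

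The model should contain baseline covariates only. The highest tacrolimus level in the first week arises after randomisation and should be left out. Nephrotoxic drug use should enter only as recorded before transplantation, since the Data collection section also records it over the first 7 days.

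The cost is a sentence or two of text and a few lines of code. No new data are needed, and N = 174 does not change.

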antibiotic prophylaxis in the first 24 hours after surgery; use of nephrotoxic
drugs in the first 7 days; immunosuppression in the first 7 days and maximum
tacrolimus level within 7 days; new surgery within 7 days after randomization;
ICU readmission for treatment of complications within 7 days after
randomization; need for retransplantation within 28 days and ICU and hospital
outcome in 28 days (discharge, hospitalization or death).

Data collection will be performed by an external professional (research nurse)
with no connection to the unit. This professional will have access to the data
described but will not have any role in the randomization and management of
patients participating in the study. Such data will be collected in an
electronic form via Redcap® and will remain protected by a
nontransferable password. The professional will perform serial evaluations to
ensure the follow-up of all patients until the 28th postoperative day. The final
result collected will be available, also by means of a password, to the external
professional in charge of the statistical calculations, as well as to the main
researcher.

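### The adjustment model treats maximum first-week tacrolimus as a baseline factor although it is measured after randomisation, and leaves the time window for nephrotoxic drugs open, so the adjusted treatment effect can be biased.

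*Protocol article*

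**What the plan says.** All of the following is in the protocol article.

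- **Statistical analysis, unadjusted comparison.** Analysis is by intention to treat. For categorical outcomes: "Categorical variables will be evaluated using the chi-square test", with Fisher's exact test as the alternative.
- **Statistical analysis, adjustment.** Results are to be corrected for renal function before transplantation, and a logistic model takes in further covariates. The section describes these as sources of "inconsistency in the baseline that were not corrected by the randomization of" LIVER-PAM. The factors named in brackets are "use of nephrotoxic drugs, maximum tacrolimus level in the first week". Two from the operation itself complete the list: "intraoperative fluid balance and intraoperative major bleeding".
- **Randomization and blinding.** The sentence on timing opens: "Patients will be randomized within 2 hours of ICU admission after liver". The interventions are not blinded.
- **Data collection.** Nephrotoxic drug use appears twice: among the preoperative items, for the week before transplantation, and among the postoperative items, where the list includes "drugs in the first 7 days; immunosuppression in the first 7 days and maximum". The last word of that extract refers to the tacrolimus level, over the same 7 days.
- **General management (both groups).** The surgical team sets initial and subsequent immunosuppressive doses, following the institutional protocol.

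**The concern.** Covariate adjustment in a randomised trial is safe when the covariates are fixed before allocation, because the arm cannot have influenced them. A covariate measured afterwards may be a consequence of the arm, of the outcome, or of both. Conditioning on it can remove part of the real effect, or create an association where none exists.

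The plan describes its covariates as baseline differences, yet at least one is not a baseline variable. Exposure to tacrolimus and other nephrotoxic drugs is also closely tied to the renal outcome under study. At stake is whether the adjusted estimate for 7-day renal dysfunction still describes the effect of the blood pressure target.

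**Working it through.** **Step 1. Place each covariate in time.** The reference point is randomisation, after surgery and within 2 hours of ICU admission.

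| Covariate in the Statistical analysis section | When recorded (Data collection or the covariate's own wording) | Before randomisation? |
|---|---|---|
| Previous renal function | Preoperative creatinine | Yes |
| Intraoperative fluid balance | During surgery | Yes |
| Intraoperative major bleeding | During surgery | Yes |
| Nephrotoxic drugs | Week before transplantation, and also first 7 days after | Depends on the record used; not stated |
| Maximum tacrolimus, first week | Postoperative, within 7 days | No |

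The primary outcome is assessed over 7 days (Main objective). Maximum tacrolimus is therefore observed alongside the outcome, during and after the 24-hour intervention. It cannot be a baseline difference that randomisation failed to correct.

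**Step 2. Is there a route to bias?** The trial is open-label, dosing decisions continue after allocation, and creatinine is collected daily. A route from arm, or from rising creatinine, to drug exposure is plausible. No passage shows that it operates.

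**Step 3. The plan's own figure.** The sample size rests on 73.7% v 53.7% (a 20-point absolute reduction), power 80% and alpha 5%, taken here as two-sided. With unpooled variance:

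n per arm = (1.960 + 0.842)² × [0.737 × 0.263 + 0.537 × 0.463] / 0.20² = 7.849 × (0.1938 + 0.2486) / 0.04 = 86.8, so 87 per arm and 174 in total.

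The stated figure is reproduced. It uses no covariates, so this point does not change it.

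**Step 4. What could happen (illustration only).** Large simulated samples with a control risk of 73.7%. The covariate T has residual SD 1. In the last two rows and the first, and in the no-effect row, an unmeasured severity factor affects both T and renal dysfunction. Every effect on T is assumed; none comes from the documents. The adjusted figure is the risk difference averaged over the sample from a logistic model with arm and T.

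| Assumed mechanism | Unadjusted risk difference | Adjusted for T | Shift (points) |
|---|---|---|---|
| Arm does not affect T | -16.2 | -16.2 | 0.0 |
| Arm lowers T by 0.5; T raises risk; no shared cause | -20.2 | -14.8 | +5.4 |
| No effect of arm on the outcome; arm lowers T by 0.5; shared cause | 0.0 | +2.9 | +2.9 |
| Arm lowers T by 0.5; T raises risk; shared cause | -17.0 | -9.7 | +7.3 |
| Arm raises T by 0.5; T raises risk; shared cause | -11.3 | -18.3 | -7.0 |

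A separate case lets renal dysfunction itself lower tacrolimus by 2, 3 or 4 ng/mL (assumed SD 4). A risk difference of -19.7 points then becomes -18.7, -17.5 or -16.0 after adjustment. The odds ratio given T stays at about 0.41 to 0.42, and when there is no treatment effect the adjusted difference stays at zero. Feedback from the outcome alone therefore attenuates the risk difference but does not create a false effect.

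**Step 5. Which covariates enter?** The section names its candidates in advance but ties the adjustment to factors showing inconsistency at baseline. One reading is that this merely describes the list. Another is that observed imbalance decides which of the named factors enter. The text gives no threshold and does not settle the matter.

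**The case against.** Several counter-arguments have force.

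- **An unadjusted intention-to-treat comparison is planned in the same section, and 174 follows from an unadjusted formula.** This stands. A reader might infer that the primary comparison as a whole loses the protection of randomisation. The documents do not support that: the problem lies in the adjusted analysis. Equally, the text does not exempt the primary outcome from adjustment or say which result decides.
- **Dosing follows an institutional protocol, and nothing says that tacrolimus differs by arm or is changed in response to creatinine.** This stands. The bias is possible, not shown.
- **The simulated sizes are hypothetical and modest.** This also stands. At 87 per arm the standard error of the risk difference is √[(0.1938 + 0.2486)/87] = 0.071, or 7.1 points. The shifts in Step 4 are mostly below this and at most about equal to it. Unlike sampling error, though, a bias does not average out and is not covered by the confidence interval.
- **The nephrotoxin term may well mean the pre-transplant record.** That reading fits the word baseline. It is an ambiguity to close, not a demonstrated error.
- **A reader might count three competing p-values, or treat entry by imbalance as a definite rule.** Both are readings. Adjustment for renal function and for the other factors shares one sentence and may be a single model. The order of analyses may also be set in an analysis plan that is not shown.

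None of this answers the timing of tacrolimus, which is fixed by the article itself.

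**Conclusion.** The plan is wrong as written on one covariate and unclear on a second. Maximum first-week tacrolimus is presented as a baseline factor but arises after randomisation, in the outcome window. Nephrotoxic drug use has both a pre- and a post-randomisation record, and the model does not choose between them. Previous renal function and the two intraoperative terms are sound.

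The adjusted treatment effect can be biased towards or away from benefit. The size cannot be known from the documents; the shifts of 0 to about 7 points are illustrations that depend entirely on assumed mechanisms. There is no such bias if allocation does not affect these exposures, either directly or through the renal outcome. It would go too far to say that the trial's main result will be biased or that its 5% error rate is lost.

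**What to change.** Change the wording of the Statistical analysis section before the allocation is revealed to the analyst:

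1. Delete maximum first-week tacrolimus, and any drug exposure after randomisation, from the adjustment model. Report these descriptively by arm.
2. Define the nephrotoxin covariate as use in the week before transplantation, which is already collected.
3. Enter a fixed set of covariates, whatever imbalance is observed: previous renal function, pre-transplant nephrotoxic drugs, intraoperative fluid balance and intraoperative major bleeding.
4. State which single analysis of the 7-day primary outcome is confirmatory. An unadjusted test and a model with pre-randomisation covariates are both defensible; the choice has to be made in advance.

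The cost is the loss of a tacrolimus-adjusted result. No new data are needed and the sample size stays at 174.
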